### 4.3 Exclusion criteria

- 4.3.1 Congenital heart disease, valvular heart disease, angina pectoris, myocardial infarction, myocarditis, cardiomyopathy, pulmonary heart disease, serious infections, autoimmune diseases, diseases of the blood system, malignant tumors; and
- 4.3.2 Combination of other arrhythmias, such as atrioventricular tachycardia, atrioventricular nodal tachycardia, preexcitation syndrome, atrioventricular block, and sick sinus node syndrome.
- 4.3.3 Previous history of percutaneous coronary intervention or transcatheter RFCA/cryoablation for atrial fibrillation;
- 4.3.4 Heart function (New York Heart Association Function Classification, NYHA) Class III or above, or left ventricular ejection fraction (LVEF) shown by color Doppler echocardiography  $\leq 35\%$ ;
- 4.3.5 Left atrial or LAA thrombus (confirmed by TEE or CTA);
- 4.3.6 Presence of serious neurological disorders (neurological infections, etc.), mental disorders (including substance abuse, chronic alcoholism, etc.).
- 4.3.7 Abnormalities of thyroid function not controlled by combined medications; and
- 4.3.8 Complicated with abnormal liver function (AST or ALT > 3 times the upper limit of normal) or abnormal renal function (SCR > 3.5mg/dl or CCr < 30ml/min);
- 4.3.9 History of cardiac surgery within the last 6 months;
- 4.3.10 Contraindications to radiofrequency ablation procedures (e.g., pregnancy status, allergy to contrast media, etc.).
- 4.3.11 A life expectancy of less than 12 months;
- 4.3.12 Participation in other clinical studies within 3 months prior to the date of informed consent, or ongoing participation in other clinical studies.

### 4.4 Abscission criteria

- 4.4.1 Enrolled patients failed to complete treatment by the enrolled treatment program due to lack of efficacy of drugs, cost of treatment, and unsuccessful surgery.
- 4.4.2 Failure to complete TEE and dynamic electrocardiogram examination at the specified time point.

### 4.5 Removal criteria

4.5.1 Those who do not follow the enrolled treatment regimen and who violate the provisions of the regimen for combining medications; and

4.5.2 Incomplete clinical information affects the judgment of test results; and

4.5.3 Intracardiac echocardiography (ICE) is used instead of TEE to guide surgery and follow-up assessment due to intolerance of TEE examination during and after surgery.

## 5. Study design

### 5.1 Study type

This study is a prospective, multicenter, randomized, controlled, and registry study (registration number ChiCTR2000031486).

### 5.2 Duration of the study

5.2.1 The duration of the study is 2 years, from 1 July 2020 to 30 June 2022.

5.2.2 Six months for ethical approval and coordination for all centers.

5.2.3 Patient enrollment at each center will last approximately 6 months, from July 1, 2020 to December 31, 2020.

5.2.4 Twelve months from enrolment to the last follow-up for all patients in the study; if necessary, the follow-up period should be extended to 2 years or more to assess the long-term outcomes.

5.2.5 Outpatient TEE or CTA reexamination on the 45th day after operation, and follow up at 6 months after operation or 3 months after adjusting anticoagulation regimen if necessary (see 8.9.3.7 for details);

5.2.6 The RFCA blanking period of AF is 3 months after operation. An outpatient follow-up visit at 3, 6, and 12 months postoperatively, and then every 6 months thereafter, for assessment of postoperative cardiac rhythms, medication records, echocardiographic evaluations, and records of adverse events (see section 8.1 for more details);

5.2.7 Patients may withdraw from the study at any time during the study for any reason. If a patient withdraws from the study, please refer to Section 8.4 Early Termination Procedures for Enrolled Patients for documentation.

### 5.3 Multicenter settings

A total of 14 centers nationwide were enrolled in this study, and the operators in each center had considerable experience in combined surgery for AF, and the volume of combined surgery for AF in a single center was no less than 50 cases.

### 5.4 Enrollment modalities

Enrollment in each subcenter could begin after study initiation and completion of subcenter ethical approval, and the enrollment period was approximately 6 months.

In this multicenter study, the number of cases enrolled in a single center will not exceed 30% of the total planned number of cases (i.e., 61 cases), and the enrollment will be stopped once the upper limit is reached.

### 5.5 Study workflow

[figure not shown]

## 6. Study tools

### 6.1 Main tools

- WatchmanTM left atrial appendage occlusion device (Boston Scientific, St. Paul, MN)
- Saline-irrigated contact-force sensing ablation catheter (Biosense Webster, Diamond Bar, CA);
- 3D electroanatomic mapping system: Carto3 system (Biosense Webster, Diamond Bar, CA, including ablation index software module);

### 6.2 Other tools

- Radiofrequency ablation system (SmartAblate, Biosense Webster, Diamond Bar, CA);
- Decapolar coronary sinus electrode catheter;
- Multipole mapping electrode catheter (LassoSAS Nav or Pentaray catheter, Biosense Webster, Diamond Bar, CA)
- Transthoracic echocardiography (TTE) and transesophageal echocardiography (TEE);
- 24-hour ambulatory electrocardiogram or 7-day ambulatory electrocardiographic monitoring.

## 7. Sample size calculations

In this study, 202 AF patients from 14 centers in China who were referred to undergo a combined procedure of LAAO combined with radiofrequency ablation were enrolled. Calculate the formula according to the sample size, with a 1:1 grouping ratio,  $N1=N2=2 [(t_{\alpha/2} + t_{\beta/2}) \delta / \sigma]^2 (\alpha=0.05, 1-\beta=0.8)$  and Study data of intergroup differences in our previous single-center, retrospective study. The sample size required for each group was calculated to be 71 cases, and the minimum sample size required for each group was 89 cases, taking into account a 20% lost rate of follow-up. Taking other factors into consideration, 101 cases were planned to be enrolled in each group.

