### **1.3 The impact of different combining strategies on clinical outcomes**

At present, the study on the optimization of combining strategy for combined treatment of AF is very limited, and there is no conclusion on whether the combined treatment with Watchman occluder should adopt the strategy of ablation first or occlusion first.

In the past, many combined studies using the Watchman occluder have used the combining strategy of ablation first followed by occlusion. The combining strategy was not discussed. Walker et al. found that reexamination of transesophageal echocardiography (TEE) 45 days after combined treatment of AF found that some patients had a newly detected peri-device leak (PDL) of no more than 3mm, which may be related to the combining strategy of ablation followed by occlusion. Our retrospective study of 82 combined cases found that when using the Watchman occluder, the proportion of newly detected PDL after the operation with the occlusion-first strategy was significantly lower than that with the ablation-first strategy. If AF ablation is performed first during the operation, the ridge between the left superior pulmonary vein (LSPV) and LAA will produce acute tissue edema. At this time, the LAA sizing and occluder selection are according to conventional standards. Although the occluder can achieve complete occlusion immediately, newly detected PDL may be generated after the tissue swelling subsides, which may even affect the stability of the occluder. However, some scholars found through intraoperative ultrasound tests that there was still a certain distance between the outer edge of the Watchman occluder and the edematous tissue at the ridge after it was expanded, so it was not sufficient to explain the generation of newly detected PDL only by the regression of edema. If the occlusion-first strategy is adopted, there is no interference of tissue edema caused by ablation, and there is no influence on the choice of occluder and compression ratio; however, some scholars are concerned that this will affect the catheter operation of subsequent ablation, and we hold a different viewpoint in this regard.

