## 3. Study endpoints

### 3.1 Primary endpoints

The primary endpoint was defined as the composite of thromboembolic events such as stroke/transient ischemic attack (TIA), device-related thrombosis (DRT), clinically relevant bleedings, and cardiovascular death or rehospitalization.

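### Section 7's 71 per arm and 80% power are not supported for the primary composite: the formula is inconsistent, and its endpoint and inputs are not stated

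*Protocol*

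**What the plan says.** Protocol Section 7 prints the formula "N1=N2=2 [(t_{\alpha/2} + t_{\beta/2}) \delta / \sigma]^2" with "\alpha=0.05, 1-\beta=0.8" and "with a 1:1 grouping ratio". The symbols are not defined. The input is described only as "Study data of intergroup differences in our previous single-center, retrospective study". The result is "The sample size required for each group was calculated to be 71 cases", raised to 89 for 20% loss to follow-up and then to 101 for unspecified other factors, 202 in total.

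Section 1.3 describes the source study: 82 combined cases, in which "the proportion of newly detected PDL after the operation with the occlusion-first strategy was significantly lower than that with the ablation-first strategy". It gives no rates and reports no other between-group difference from that study.

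Section 3.1 defines the primary endpoint as the "composite of thromboembolic events such as stroke/transient ischemic attack (TIA), device-related thrombosis (DRT), clinically relevant bleedings, and cardiovascular death or rehospitalization". PDL is not a component. Section 9 compares this endpoint between groups by Kaplan-Meier analysis. No event rate or target effect for the composite appears in the protocol.

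**The concern.** A sample size statement should connect an endpoint, an assumed effect, a test and a power. Here the chain breaks in two places.

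- **The formula disagrees with the line it stands in.** The beta/2 quantile does not match the stated 80% power, and the ratio of delta to sigma makes the required number rise with the effect if the letters carry their usual meaning.
- **Nothing links the calculation to the primary endpoint.** The formula compares two means, the source study is reported only for leak, and the primary analysis is time to first clinical event.

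Section 7 holds the protocol's only power statement, so readers will apply its 80% to the primary comparison. A non-significant result would then be read against a power that was never derived for that endpoint.

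**Working it through.** **Inputs from the protocol.** Alpha 0.05, with an alpha/2 quantile and so two-sided; power 0.80; 1:1 allocation; 71, 89 and 101 per arm; 20% loss (all Section 7). Composite endpoint without PDL (Section 3.1). Kaplan-Meier comparison (Section 9). Twelve months of follow-up (Section 5.2). Delta, sigma and event rates are not given. Normal quantiles are used below: 1.960 for alpha/2, 0.842 for 80% power, 1.282 for 90% power.

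**1. The loss step reproduces.** 71 / (1 − 0.20) = 88.75, rounded up to 89.

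**2. The beta quantile.** With beta = 0.2, beta/2 = 0.1 and the quantile is 1.282, which belongs to 90% power. The effect on n is [(1.960 + 1.282) / (1.960 + 0.842)]² = 1.34. If beta/2 was really applied, 71 is the number for 90% power, and 80% would need about 71 / 1.34 = 53.

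**3. The direction of the ratio.** The standard form is n = 2[(1.960 + 0.842) × sigma/delta]². As printed, with delta/sigma and the 80% quantile:

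| delta/sigma | n as printed | n in standard form |
|---|---|---|
| 0.5 | 4 | 63 |
| 1.0 | 16 | 16 |
| 2.0 | 63 | 4 |

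**4. Can 71 be traced?** In standard form it needs a standardised difference of about 0.47, since 2 × (2.802 / 0.47)² = 71.1, or about 0.545 with the beta/2 quantile. As printed it needs a ratio of about 2.13 or 1.84. A two-proportion formula gives 71 for many pairs, among them 17% vs 3%, 27% vs 9%, 34% vs 14% and 44% vs 22%. The figure 71 therefore does not identify its inputs.

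**5. Power for the composite under assumed rates.** No rate is documented, so the control rates below are assumptions, each with the risk halved. Two-proportion normal approximation, two-sided 0.05:

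power = Φ{ [ |p1 − p2| √n − 1.960 √(2 p̄(1 − p̄)) ] / √( p1(1 − p1) + p2(1 − p2) ) }

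Example, 20% vs 10% with 81 per arm: (0.10 × 9 − 1.960 × 0.505) / 0.5 = −0.18, so power is 0.43. The 81 is 101 × 0.8 = 80.8.

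| Assumed rates | 71 per arm | 81 per arm (101 less 20%) | 101 per arm (no loss) |
|---|---|---|---|
| 10% vs 5% | 20% | 22% | 27% |
| 20% vs 10% | 38% | 43% | 51% |
| 30% vs 15% | 57% | 63% | 73% |
| 40% vs 20% | 74% | 80% | 88% |

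**6. On the time-to-event scale.** The Schoenfeld formula for a hazard ratio of 0.5 gives 4 × (2.802)² / (ln 0.5)² = 65.3, so 66 events in total. That is 66 / 202 = 33% of all patients, or 66 / 162 = 41% of the 2 × 81 left after loss.

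**The case against.** Much can be said for the protocol, and several stronger readings that a reader might infer do not stand.

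- **That 71 came from an inverted formula.** The symbols are undefined, and swapping the two letters restores the standard form. A typing or translation error is a fair explanation, and nothing shows that 71 was computed as printed.
- **That the beta/2 slip weakens the trial.** It works the other way: if applied, it enlarged n and gave 90% power. It is an inconsistency, not a cause of low power.
- **That a two-means form is wrong in itself.** With sigma² = p(1 − p) it is a usual approximation for two proportions, so the form alone does not exclude an event endpoint. The missing inputs matter more.
- **That 71 was calculated for PDL.** Section 7 does not say so. Section 1.3 discusses leak and would naturally cite only the leak result, and the source study may have compared other outcomes. PDL is an inference.
- **That the trial can detect only a very large effect.** This holds only at low to moderate event rates. The composite includes clinically relevant bleeding and rehospitalization, so a high rate cannot be excluded, and halving a 40% rate has about 80% power even after 20% loss.

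It might also be said that such detail belongs in an analysis plan. But the protocol has its own sample size section, and the inconsistency is printed there. After all these concessions, the stated 80% still has no documented basis for the primary comparison.

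**Conclusion.** The point holds in this form: 71 per arm and 80% power are unsupported for the primary endpoint. That conclusion rests on the text alone and needs no assumed rate. The formula is inconsistent with its stated power, and inverted in conventional notation. The endpoint and inputs behind 71 are absent. The only difference reported from the source study concerns an outcome outside the composite.

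The size of any shortfall cannot be fixed from the documents. With the risk halved and 81 per arm, power runs from about 22% to about 80% as the assumed control rate goes from 10% to 40%. These figures use a two-proportion approximation to the planned Kaplan-Meier comparison. Power for the primary comparison is therefore unknown and may be low; the documents do not show that 101 per arm is too few.

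**What to change.** Rewrite Section 7 as follows, without adding patients.

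1. Correct the formula (the quantile for 80% power, the effect in the denominator, symbols defined), or replace it with one that matches the endpoint.
2. Name the endpoint and give the inputs that produce 71. If the endpoint is PDL, state the two proportions from the retrospective study and use a two-proportion formula.
3. For the primary composite, state an assumed 12-month event rate and report the power, or the detectable hazard ratio, with 202 patients and 20% loss. Show a range if the rate is uncertain.
4. Attribute the 80% only to the endpoint it was calculated for. Keep it for the composite only if step 3 supports it.

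The cost is protocol wording and a short recalculation. No visit, procedure or enrolment target changes. The power stated for the primary endpoint may turn out lower than 80%, depending on the rate and effect assumed.

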## 8. Description of the Study protocol

### 8.1 Study Program - Overview

Table 1 - Overview of the study process

| Event                     | Time                                                                        | Windows        | Matters                                                                                                                                                                                                                                                                                                                                                                                                                                                                                                                                                                                                                                                                                                                                                                                                                              |
|---------------------------|-----------------------------------------------------------------------------|----------------|--------------------------------------------------------------------------------------------------------------------------------------------------------------------------------------------------------------------------------------------------------------------------------------------------------------------------------------------------------------------------------------------------------------------------------------------------------------------------------------------------------------------------------------------------------------------------------------------------------------------------------------------------------------------------------------------------------------------------------------------------------------------------------------------------------------------------------------|
| Enrollment         | Within 14 days prior to the baseline visit or at the time of the visit, the | Not applicable | 
 
Judging criteria for admission to the platoon
 
informed consent of the patient
 
                                                                                                                                                                                                                                                                                                                                                                                                                                                                                                                                                                                                                                                                                             |
| Baseline visits    | Within 2 weeks prior to the combined surgery                                | Not applicable | 
 
baseline information and physical examination
 
Assessment of stroke risk (CHA2DS2-VASc score) and bleeding risk (HAS-BLED score)
 
history of atrial fibrillation
 
history of prior stroke/thromboembolism/bleeding
 
History of comorbid cardiovascular diseases such as hypertension/heart failure/cardiomyopathy, diabetes mellitus, and peripheral vascular disease
 
Medication history (including oral antithrombotic drugs §, AAD)
 
12 lead ECG and/or 24h Holter ECG data
 
TTE assessment (LA, LVEDd, LVEDs, LVEF)
 
TEE or CTA to exclude thrombus
 
baseline blood counts, liver function, renal function, coagulation, troponin, cardiac enzyme profile
 
             |
| Randomization      | After signing the informed consent form, prior to surgery                   | Not applicable | 
 
Uniform computerized randomization of core laboratories, randomized grouping by serial number of enrollment
 
                                                                                                                                                                                                                                                                                                                                                                                                                                                                                                                                                                                                                                                                        |
| Combined procedure | within 30 days of the baseline visit                                        | Not applicable | 
 
Collect operation related data (anesthesia mode, operation time, X-ray fluoroscopy dose and time, contrast agent dose, etc.)
 
Collection of data related to radiofrequency ablation (including ablation procedure, ablation time, pulmonary vein isolation time, single-loop isolation, patch location, non-pulmonary vein triggered foci, ablation of combined arrhythmias, etc.)
 
Collect LAAO related data (multi position angiography and measurement results, whether to use the "steel ball method" for positioning, intraoperative ultrasonic measurement results, number and size of occluders, times of deployment and recovery, maximum diameter/compression ratio of occluder after release, marginal shunt, and pull test)
 
Adverse events (*)
 
 |
| 1st visit          | 12h after operation ~ before discharge                                      | Not applicable | 
 
postoperative 12-lead electrocardiogram
 
Postoperative renal function, coagulation, troponin, cardiac enzyme profile
 
Color ultrasound of pericardial cavity after operation (can be completed within 12 hours after operation)
 
Adverse events (*)
 
                                                                                                                                                                                                                                                                                                                                                                                                                                                                                                        |

|                            |                           |           |                                                                                                                                                                                                                                                                                                                                                                                                         |
|----------------------------|---------------------------|-----------|---------------------------------------------------------------------------------------------------------------------------------------------------------------------------------------------------------------------------------------------------------------------------------------------------------------------------------------------------------------------------------------------------------|
| 2nd visit           | 45 days after procedure   | ± 7 days  | 
 
• TEE follow-up evaluation of occluder #
 
• 12-lead electrocardiogram
 
• Adverse events (*)
 
                                                                                                                                                                                                                                           |
